#### Exclusion criteria

1) Serious physical diseases that hinder completion of the cognitive function screening. Such as severe Parkinson, paralysis and so on. 2) Drug or alcohol dependence. 3) Other nervous system diseases and/or serious medical conditions that can alter brain function. 4) Inability to use smartphones independently.

### Sample size calculation

The required sample size is estimated using PASS v11.0 (NCSS, Kaysville, UT, USA) based on a completely random design for comparing the means of two independent samples. To our knowledge, there is no previous study on a stratified support pattern-based internet-assisted self-management therapy for DM-MCI in mainland China, so we estimate the effect size of one of the outcomes (HbA1c) based on previous research on patients with DM-MCI [42]. This study find that HbA1c scores in intervention and control group are 6.49 ± 1.59 and 6.97 ± 0.73, respectively. A sample size of 34 participants per group was determined to be sufficient to detect an effect with a type 1 error rate of 5% (α = 0.05) and 90% power (β = 0.1). A total of 68 participants will be needed, with 34 participants per group. Considering a 20% loss of follow-up rate, the final sample size is 86, with 43 participants per group.

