**Methods:**

Eighty-four DM-MCI patients will be randomly divided into an intervention group and a control group in a 1:1 ratio. The intervention group will receive a self-management intervention using the stratified support pattern-based internet-assisted therapy (SISMT), while the control group will receive the health manual intervention (HMI). The study recruiter will be blinded to the group allocation and unable to foresee which group the next participant will be assigned to. At the same time, the allocation will be also hidden from the research evaluators and participants. After 12 weeks and 24 weeks, cognitive function, blood glucose, self-management ability, psychological status, health literacy, and self-management behavior of patients in both groups will be measured and compared.

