#### Primary outcomes

The primary outcome measures will be general cognitive function (MoCA [35], MMSE [36]).

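### The 34 per group at 90% power does not follow from the stated HbA1c inputs, which give about 35% power and need about 141 per group; HbA1c is also not the primary outcome

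*Protocol article*

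**What the plan says.** The Sample size calculation section names PASS v11.0 and a calculation "based on a completely random design for comparing the means of two independent samples". Because the authors know of no earlier study of this therapy in this population in mainland China, they write: "so we estimate the effect size of one of the outcomes (HbA1c) based on previous research on patients with DM-MCI". The inputs are given as "HbA1c scores in intervention and control group are 6.49 ± 1.59 and 6.97 ± 0.73, respectively", with a type 1 error rate of 5% and 90% power. Whether the test is one- or two-sided is not stated.

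The result follows: "A sample size of 34 participants per group was determined to be sufficient to detect an effect". That makes 68 in total. After allowing for 20% loss to follow-up, "the final sample size is 86, with 43 participants per group".

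Two other places bear on this:

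- Primary outcomes: "The primary outcome measures will be general cognitive function", measured by MoCA and MMSE. HbA1c is listed under Secondary outcomes.
- Abstract, Methods: "Eighty-four DM-MCI patients will be randomly divided", which is 84 and not 86.

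**The concern.** Apart from sidedness, the section gives everything needed to repeat the calculation. The cited difference is less than half a pooled SD, and 34 per group is too few to detect an effect of that size with 90% power.

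A reader told that the trial has 90% power will treat a non-significant HbA1c result as informative. On the stated inputs, the trial would miss the cited difference about two times in three. The statement also says nothing about cognition, which is the primary objective, so the article gives no basis for judging what a null result on MoCA or MMSE would mean.

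**Working it through.** **Inputs** (all from Sample size calculation): means 6.49 and 6.97; SDs 1.59 and 0.73; α = 0.05; power 90%; equal groups; stated result 34 per group. I assume a two-sided test and also show one-sided.

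**Effect size**

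- Difference: 6.97 − 6.49 = 0.48.
- Pooled SD: √[(1.59² + 0.73²)/2] = √[(2.528 + 0.533)/2] = 1.237.
- Standardised difference: d = 0.48/1.237 = 0.388.

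**Attempt to reproduce 34 per group**

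Normal approximation: n per group = 2(z₁₋α/₂ + z₁₋β)²/d² = 2(1.960 + 1.282)²/0.388² = 2 × 10.507/0.1505 = 139.6, so 140. The exact t-test gives 140.6, so 141. Welch's test, which allows the unequal SDs, also gives 141.

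Other readings, using the t-test at 90% power:

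| SD used | Two-sided n per group | One-sided n per group | Two-sided power at 34 |
|---|---|---|---|
| Pooled, 1.237 | 141 | 115 | 35% |
| Simple average, 1.16 | 124 | 101 | 39% |
| Larger SD in both arms, 1.59 | 232 | 189 | 23% |
| Smaller SD in both arms, 0.73 | 50 | 41 | 76% |

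Misreading the SDs as variances gives 106 two-sided or 87 one-sided (normal approximation). The nearest match is a one-sample formula without the factor 2: 10.507/0.1505 = 69.8, so 70, against the stated total of 68. That is not the two-sample design the section names. No two-sample reading at 90% power gives 34.

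**Power for the stated HbA1c difference (pooled SD)**

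- 34 per group: 35.1% two-sided (Welch 34.7%); 47.5% one-sided.
- 43 per group, with no loss: 42.8% two-sided; 55.6% one-sided.

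**What 34 per group can detect (two-sided t-test)**

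- 90% power: d = 0.80, which is 0.80 × 1.237 = 0.99 HbA1c points, about twice the stated 0.48.
- 80% power: d = 0.69, or 0.85 points.
- For a difference of 0.48 to have 90% power, the common SD would have to be 0.48/0.798 = 0.60, below both stated SDs.

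**Primary outcome**

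The article gives no SD or target difference for MoCA or MMSE, so no required n can be computed. As an illustration, with an assumed MoCA SD of 2 to 4 points and no baseline adjustment, 34 per group detects 0.69 × SD = 1.4 to 2.8 points at 80% power and 0.80 × SD = 1.6 to 3.2 points at 90%.

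**Loss to follow-up and the two totals**

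34/0.8 = 42.5, so 43 per group and 86 in total. This step is correct. With 84 enrolled, 84 × 0.8 = 67.2, so 67 completers, one short of the protocol's own 68.

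**The case against.** **The 35% is not the trial's power.** It applies only to a 0.48 difference in HbA1c. Power for MoCA and MMSE is unknown and could be higher or lower. This is right, and the power figures here are limited to HbA1c.

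**Sidedness is not stated.** Also right. The range is about 35% two-sided to 48% one-sided, and neither is close to 90%.

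**The printed inputs may be the error.** A mean or SD may have been mistranscribed from the cited study, or different values may have been entered in PASS. The document cannot settle this. It shows that inputs and result disagree, not which is wrong, so the inputs should be checked before the power is restated.

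**The planned linear mixed model uses baseline data and is more efficient than a t-test.** This does not rescue the HbA1c figure, because the section names a two-sample comparison and gives no correlation. If adjustment multiplies n by 1 − ρ², an assumed baseline to follow-up correlation of 0.8 still needs 140.6 × 0.36 ≈ 51 per group. Reaching 34 takes 1 − ρ² = 34/140.6 = 0.242, so ρ ≈ 0.87, which nothing in the article supports. The point does make the MoCA illustration pessimistic. At assumed correlations of 0.5 to 0.7, the detectable d at 90% power falls from 0.80 to about 0.69 to 0.57, or about 1.1 to 2.8 points over SDs of 2 to 4.

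**Sizing on HbA1c is disclosed, and 84 against 86 is editorial.** Both are fair. Disclosure still leaves the primary outcome without a power statement. The conflict in totals is minor and adds nothing to the arithmetic finding.

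**Conclusion.** The sample size statement is wrong as written and must be corrected. On the printed inputs, 90% power needs 141 per group two-sided (115 one-sided), about four times the stated 34. Power at 34 per group for the cited HbA1c difference is about 35% two-sided, or 48% one-sided. The gap is far beyond rounding or software differences, and it survives every choice of SD and sidedness tried.

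The result rests on the means and SDs as printed and on the two-sample comparison the section names. The choice of a two-sided test affects the size of the shortfall but not its existence. The MoCA figures rest on an assumed SD and are illustrative only. Separately, the primary outcome has no power statement, and the enrolment target needs a single value.

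**What to change.** 1. Check the HbA1c means and SDs against the cited study and the values entered in PASS, correct any transcription error, and state whether the test is one- or two-sided.
2. Withdraw the 90% power claim. If the printed inputs are confirmed, state that 43 randomised (34 completing) per group gives about 35% power, two-sided, for the cited HbA1c difference.
3. Justify the size on the primary outcome. State the MoCA difference detectable with 34 completers per group at 80% and 90% power, with the assumed SD and its source, and do the same for MMSE. If the calculation relies on baseline adjustment in the mixed model, state the assumed correlation.
4. Give one enrolment figure throughout. If 34 completers per group is kept as the target, 86 agrees with the 20% loss allowance and the abstract should say 86.

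The cost is protocol wording and a short recalculation. No extra patients are required. The stated power becomes less favourable.

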### Randomization, blinding, and concealed allocation

Ensuring allocation concealment, participants will be randomized (after obtaining written informed consent, eligibility screening, and baseline assessment) to the intervention and control groups at a 1:1 ratio by a study staff member (who will not be involved in participant recruitment or outcome assessment) using Research Randomizer software (http://www.randomizer.org/). Participants in the intervention group will be assigned to different categories of the intervention group based on their cognitive function and self-management characteristics and will receive Intervention measures with different frequencies. Participants in the control group will be assigned to different categories of the control group based on their cognitive function and self-management characteristics, too, but there is no difference in intervention frequency. The participants will then be told their group assignment by the intervention staff. Due to the nature of non-pharmacological interventions, only the outcome assessors and data analysts (not the participants or intervention staff) will be blinded to group allocation.

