### Intervention

#### Intervention group

In this study, the intervention group will adopt a SISMT. After the completion of the baseline survey, participants will formulate personalized intervention measures and optimize and expand their knowledge through hierarchical strategies to improve their self-management behavior. Based on our previous research in this study, the patients will be divided into four categories according to cognitive function and self-management ability: (1) high cognitive high management, (2) high cognitive low management, (3) low cognitive high management, and (4) low cognitive low management. Four WeChat groups will be formed to intervene separately to prevent communications between each category of participants in the intervention group. Self-management interventions targeted to patients with DM-MCI will be implemented, including diet, exercise, drug intake, psychology, and cognition. To achieve stratified intervention with different intensity, the content will remain the same for each group, but the frequency will differ. The intervention plan is shown in Table 1. All intervention content will be implemented through home self-monitoring and WeChat feedback. When patients experience suboptimal blood sugar monitoring, researchers will guide them in regulating self-management behavior. If behavioral regulation is ineffective, contact the attending physician for medication guidance. The outcome indicators will be collected at three time points: baseline, 12 and 24 weeks, respectively.

**Table 1 Tab1:** Intervention plan of the the stratified support pattern-based internet-assisted self-management therapy for DM-MCI

Patient type	Intervention method	Specific content

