### Statistical analysis

All data analysis will be performed using SPSS Statistics v21.0 (IBM). To ensure that they are blinded to group assignment, the outcome assessors and data analysts will not interact with the participants except during data collection (in the case of outcome assessors). Demographic and other baseline characteristics will be summarized using descriptive statistics. If necessary, the results will be adjusted for potential confounders, such as age, gender, and education. Quantitative data will be expressed as frequencies or rates and statistical analysis will be carried out using the *χ*^2^ test. If these data are normally distributed, they will be expressed as (*x* ± *s*). The effects of the interventions (between-group differences) will be calculated with linear mixed models using interaction terms (group allocation versus time), which are equivalent to the between-group differences. The within-group differences will be calculated using repeated measures ANOVA. *P*-values < 0.05 will be considered statistically significant. The data will be reviewed before analysis. The Statistical Package for the Social Sciences (SPSS) software will be used for all analyses. The clinical relevance of the results will be confirmed by calculating the effect size (Cohen d) of the significant differences found between the assessments. The following effects will be considered: small: 0.00–0.49; medium: 0.50–0.79; high ≥0.80 (Cohen, 1988). Comparison between the four subgroups within the intervention group using ANOVA test.

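### Allocation is not described as stratified by the four cognition/self-management classes, and neither class nor baseline cognition is a named covariate: valid, but it gives up balance and precision that cost little to secure

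*Protocol article*

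**What the plan says.** Under Randomization, blinding, and concealed allocation, "participants will be randomized (after obtaining written informed consent, eligibility screening, and baseline assessment) to the intervention and control groups at a 1:1 ratio"; a staff member outside recruitment and assessment does this "using Research Randomizer software". No strata, blocks or minimisation are mentioned. The Sample size calculation section is "based on a completely random design for comparing the means of two independent samples".

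Classing is described after that, separately in each arm. In the SISMT arm, "Participants in the intervention group will be assigned to different categories of the intervention group based on their cognitive function and self-management characteristics", with intensity following the class. Controls are classed in the same way, "but there is no difference in intervention frequency". The Intervention group section gives the classes: "the patients will be divided into four categories according to cognitive function and self-management ability", that is, high or low on each. Cognition (MoCA, MMSE) and self-management (DSCS) are both already measured at screening.

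The primary outcomes are MoCA and MMSE, collected at baseline, 12 and 24 weeks. Under Statistical analysis, the treatment effect is the group-by-time term of a linear mixed model. Covariate adjustment is left to be made where needed, with age, gender and education as examples. The only stated analytic use of the classes is "Comparison between the four subgroups within the intervention group using ANOVA test".

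**The concern.** The classes are the feature on which SISMT is built. They rest partly on baseline cognition, which is measured on the same scales as the primary outcome, and they can be known before anyone is allocated. Yet the described procedure uses them neither to balance the arms nor in the between-arm model. With about 43 per arm, the mix of classes and the mean baseline score can differ noticeably by chance. The analysis as worded leaves it open whether either will be adjusted for.

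At stake are the precision of the primary contrast and its error given the imbalance that happens to arise. An open-ended trigger for adjustment also leaves the choice of model until after the data are seen.

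**Working it through.** **Inputs from the article.** 34 per group before dropout and 20% loss: 34/(1 − 0.20) = 42.5, rounded up to 43, so 86 in total. This reproduces the stated final size (the abstract says 84; 86 is used here). There are four classes and 1:1 allocation.

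**Assumptions, not in the article.** Class sizes; baseline-to-follow-up correlation ρ from 0.3 to 0.8; normal scores; for class, median splits with self-management unrelated to later cognition.

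**1. Class imbalance.** For a 43:43 split, the numbers d₁…d₄ falling in one arm have probability Π C(N_k, d_k) / C(86, 43). This was evaluated by simulation (200,000 draws).

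| Class sizes | Some class splits 2:1 or worse | Low-cognition share differs by ≥10 points |
|---|---|---|
| 22/22/21/21 | 33% | 28% |
| 35/25/16/10 | 45% | 24% |

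The 10-point figures are sensitive to rounding. Ten points of 43 is 4.3 people, and with 42 or 44 low-cognition participants the count difference must be even, so 6 is needed; with an odd total, 5 would do. A second model (independent draws in each arm, four equal classes) gives a 63% chance that some class share differs by at least 10 points, 32% for 15 points and 12% for 20 points.

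**2. Baseline score imbalance.** The standard error of the standardised difference is √(2/43) = 0.216. Then P(|D| ≥ 0.25 SD) = 2[1 − Φ(0.25/0.216)] = 0.25, and P(|D| ≥ 0.5 SD) = 0.02.

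**3. What reaches the contrast.** With true effect δ and chance baseline difference D, the expected follow-up difference is δ + ρD. With complete data the group-by-time contrast is the difference in change, so it has expectation δ + (ρ − 1)D. Simulation under the null (20,000 trials, 34 per arm) gave:

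| ρ | Shift in change contrast per unit D | Shift after baseline adjustment | Variance, change | Variance, adjusted | Cut in SE |
|---|---|---|---|---|---|
| 0.3 | −0.70 | about 0 | 0.0830 | 0.0544 | 19% |
| 0.5 | −0.50 | about 0 | 0.0588 | 0.0449 | 13% |
| 0.7 | −0.30 | about 0 | 0.0351 | 0.0301 | 7% |
| 0.8 | −0.20 | about 0 | 0.0235 | 0.0216 | 4% |

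The last column is 1 − √(adjusted/change); for ρ = 0.3, 1 − √(0.0544/0.0830) = 0.19. A baseline difference of 0.25 SD, which has a one-in-four chance of being reached, therefore moves the contrast by 0.25 × 0.2 = 0.05 SD to 0.25 × 0.7 = 0.175 SD.

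**4. Type I error.** Averaged over randomisations, the unadjusted analyses (follow-up only and change) rejected a true null in 0.048 to 0.053 of trials.

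**5. Class alone.** A median split on baseline explains (2/π)(1 − ρ)/2 of the variance of change: 0.22 at ρ = 0.3 and 0.06 at ρ = 0.8. After the cost of fitting the class terms, the simulated cut in standard error is about 10% down to 2%. Once the baseline score is in the model, class adds nothing under these assumptions.

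**The case against.** The strongest reply is that simple randomisation is valid and the planned contrast already uses the baseline score. Both points stand. A reader might infer that class imbalance biases the primary comparison, or that class confounds it because it sets intensity. The documents do not support either reading: chance imbalance is not systematic bias, type I error stays near 5%, and intensity by class is part of the SISMT strategy being tested.

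A reader might also infer that classing after allocation lets knowledge of the arm influence the primary result. The article does not say who assigns class, the inputs are scores taken before randomisation, and class is not in the between-arm model, so misclassing could not bias that contrast through the analysis.

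Nor is a larger precision gain supported. Supposing that class explains 20–30% of outcome variance beyond baseline would give 1 − √0.8 = 11% to 1 − √0.7 = 16%, but half of the class definition is baseline cognition itself, and nothing in the article suggests that self-management would supply the rest.

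Finally, an article condenses. A fuller protocol might stratify the list, and the sample-size wording about a completely random design describes the calculation rather than the list. That caveat stands. The point is still more than missing detail, because the article describes the order of allocation and classing and gives example adjustment variables that leave out the factor on which the intervention is built.

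**Conclusion.** The point holds as a moderate, inexpensive improvement in design and analysis; the trial is not invalid without it. As described, allocation makes no stated use of class, and the model commits to adjusting for neither class nor baseline cognition. Noticeable class imbalance is likely at this size. A chance baseline difference then shifts the group-by-time contrast through regression to the mean, and some precision is lost. Most of the recoverable precision comes from the baseline score; class matters mainly for balance and as the stratification factor. The sizes rest on assumed class sizes and correlations, which the article does not give, and on no stratification being specified elsewhere.

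**What to change.** 1. Derive class for everyone from the pre-randomisation cognition and DSCS scores, with cut-offs fixed in advance, before allocation.
2. Stratify the allocation list by class, using permuted blocks of varying size, held by the same independent staff member.
3. Replace the conditional adjustment with a prespecified one: the baseline MoCA or MMSE score (matching the outcome) and class. The simplest form models the 12- and 24-week scores with baseline as a covariate. If baseline stays in the outcome vector, each covariate also needs its time interaction, because a main effect alone leaves the group-by-time contrast essentially unchanged.
4. If recruitment has begun, leave the list as it is and prespecify the baseline-score and class adjustment before any arm comparison is seen.

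**Cost.** Four lists in place of one, some incomplete blocks in small classes (so balance there is not guaranteed), and extra fixed-effect parameters: 3 for class plus 3 × 2 = 6 for class by time with three visits, 9 in all, against 68 planned completers. No additional patients or measurements are needed.

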### Intervention

#### Intervention group

In this study, the intervention group will adopt a SISMT. After the completion of the baseline survey, participants will formulate personalized intervention measures and optimize and expand their knowledge through hierarchical strategies to improve their self-management behavior. Based on our previous research in this study, the patients will be divided into four categories according to cognitive function and self-management ability: (1) high cognitive high management, (2) high cognitive low management, (3) low cognitive high management, and (4) low cognitive low management. Four WeChat groups will be formed to intervene separately to prevent communications between each category of participants in the intervention group. Self-management interventions targeted to patients with DM-MCI will be implemented, including diet, exercise, drug intake, psychology, and cognition. To achieve stratified intervention with different intensity, the content will remain the same for each group, but the frequency will differ. The intervention plan is shown in Table 1. All intervention content will be implemented through home self-monitoring and WeChat feedback. When patients experience suboptimal blood sugar monitoring, researchers will guide them in regulating self-management behavior. If behavioral regulation is ineffective, contact the attending physician for medication guidance. The outcome indicators will be collected at three time points: baseline, 12 and 24 weeks, respectively.

**Table 1 Tab1:** Intervention plan of the the stratified support pattern-based internet-assisted self-management therapy for DM-MCI

Patient type	Intervention method	Specific content
High cognition, high management	1. Monitor fasting blood glucose or 2 h postprandial blood glucose 2–3 times a week and provide once a week reminders 2. Learn disease and health-related information and assess diet, exercise, medication, cognitive training, and mental health, once a week 3. Exercise 3 days a week for 20-–40 min each time and provide once a week reminders	**Dietary management:** Mediterranean cuisine, with Omega-3 as the core; Use more fruits and vegetables, fish, olive oil, nuts, beans, and coarse grains. Peanut oil, soybean oil, walnut oil and rapeseed oil can be selected as oil; Fish: Both marine and non marine fish are acceptable; It is not recommended to supplement Vitamins B, E, and complex vitamins to delay cognitive impairment. Recommend low GI foods to control or reduce weight **Exercise management:** 150 min of light to moderate aerobic exercise per week **Medication management:** Medication time, medication method, and medication contraindication **Blood glucose monitoring:** Oral hypoglycemic drugs are used to monitor fasting blood glucose or 2-h postprandial blood glucose 2–4 times a week. If blood glucose control is stable, the interval can be flexibly adjusted, and blood glucose measurement methods (Preprandial blood glucose, pre—post blood glucose matching) can be selected based on one's own blood glucose situation. Those who do not meet the standard for glycated hemoglobin should be tested every 3 months, and once every 6 months after reaching the standard **Cognitive guidance:** Knowledge of cognitive impairment diseases, prevention methods, influencing factors and so on. And appropriate reminders as cognitive stimulation. Cognitive monitoring is followed up every 12 weeks
High cognition, low management	1. Monitor fasting blood glucose or 2 h postprandial blood glucose 3 × a week and provide once a week reminders 2. Learn disease and health related knowledge and assess diet, exercise, medication, cognitive training, and mental health, twice a week 3. Exercise 3 days a week for 20–40 min and provide once a week reminders	
Low cognition, high management	1. Monitor fasting blood glucose or 2 h postprandial blood glucose 3 × a week and provide twice a week reminders 2. Learn disease and health-related knowledge and assess diet, exercise, medication, cognitive training, and mental health 3 × a week	
Low cognition, low management	1. Monitor fasting blood glucose or 2 h postprandial blood glucose 2–3 times a week and provide 3 × a week reminders 2. Provide correct disease-related knowledge and assess diet, exercise, medication, cognitive training, and mental health twice a week 3. Exercise 3 days a week for 20–40 min and provide 3 × a week reminders	
**Target range of blood glucose**	The **target of blood sugar control** is divided into three levels: strict, general, loose **The FBS is sequentially controlled as follows:** 4.4–6.1 mmol/L, 6.1–7.8 mmol/L, 7.8–10.0 mmol/L **The PBS is sequentially controlled as follows:**: 6.1–7.8 mmol/L,7.8–10.0 mmol/L,7.8–13.9 mmol/L	
**Requirements of blood sugar control**	① Strict control: Before and after elective or emergency fine surgery (such as plastic surgery) ② General control: People at high risk of cardiovascular and cerebrovascular diseases accompanied by unstable cardiovascular and cerebrovascular diseases, glucocorticoid therapy, selective large, small, and organ transplant surgeries, emergency organ transplant surgeries, surgical ICU patients ③ Loose control: People at high risk of hypoglycemia, hospitalized due to cardiovascular and cerebrovascular diseases, moderate to severe liver and kidney dysfunction, elderly people over 75 years old, life expectancy < 5 years (such as malignant tumors), mental or intellectual disabilities, before and after emergency large, small, and medium-sized surgeries, gastrointestinal or parenteral nutrition	
**Intervention implementation**	**Health knowledge learning and feedback:** □ Push disease related health knowledge in the form of official account □ Ask the patient questions related to the health knowledge pushed on that day □ Discuss key knowledge points in the group and invite patients to draw inferences from each other **Blood glucose monitoring, exercise, medication reminders:** Reminder in the form of WeChat chat box text **Interactive consultation:** Researchers establish a WeChat group where patients can discuss within the group. Participants can also send questions one-on-one to researchers for consultation	
**Intervention media**	WeChat	

